#### 2.4.4. Randomization and Blinding

The people in charge of other assignments (or independent statisticians) who are not involved in conducting and evaluating this clinical trial will generate a random assignment list in a specific and reproducible manner. Randomization of experimental group 1, group 2, and the control group will be performed with a block randomization method in a 1:1:1 ratio. The random assignment table will be sealed and kept in a way that can be checked for unsealing, managed separately by the research manager in the presence of the participants. Each group will be randomly assigned with the same probability of each individual being selected using the statistical program StataMP 16 program (StataCorp LLC, [name]). The investigators and assessors will be separated so that the assessors will not know what kind of treatment the subjects have received. It is not possible to maintain investigator blindness.

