# DJ-E-ZZZ [DJ: Daejeon Korean Medicine Hospital of Daejeon University, E: initial enrollment, ZZZ: Serial number [001, 002~]] [ex. DJ-E-014: 14th registered subjects of Daejeon Korean Medicine Hospital of Daejeon University].

Screening tests should be conducted within ten days prior to visit 1 (baseline visit) and visit 13 should be conducted within 16 weeks (±7 days). At visit 1, the investigator will check the results of the screening test (including chest X-ray and laboratory tests), physical examination, and changes in medical history and concomitant medication between the screening and visit 1. The subjects will be randomly assigned to one of three groups: experimental group 1, experimental group 2, or the control group, and each subject will be provided with a unique identification code for tracking and analysis purposes. Before the intervention, subjects will complete the Likert Scale for Major Symptoms of Hwa-Byung (HB-M), The Core Seven-Emotions Inventory Short Form (CSEI-S), Patient Health Questionnaire-15 (PHQ-15), Stress Response Index (SRI), State-Trait Anxiety Inventory (STAI), State-Trait Anger Expression Inventory (STAXI), functional Near-Infrared Spectroscopy (fNIRS) (device name: NS1-H20AM), Heart Rate Variability (HRV), efficacy analysis (EQ-5D, EQ-VAS), and cost analysis. Experimental group 1 will be treated with ETE, and experimental group 2 will be treated with VR-based ETE, while the control group will receive Hwa-Byung management training materials only. At visits 1–12, the investigator will check for adverse effects and changes in medical history and concomitant drugs and patient compliance; subjects will receive ETE or VR-based ETE according to the corresponding intervention schedule at each visit. Tests and assessments will be conducted according to the following schedule: visit 8 (efficacy analysis; EQ-5D, EQ-VAS, cost analysis); visit 12 (HB-M, CSEI-S, PHQ-15, SRI, BDI, STAXI, STAI, fNIRS, HRV, efficacy assessment; EQ-5D, EQ-VAS, cost analysis, laboratory tests); and visit 13 (follow-up visit; HB-M, CSEI-S, PHQ-15, SRI, BDI, STAXI, STAI, efficacy assessment; EQ-5D, EQ-VAS, cost analysis, physical examination, adverse effects, changes in medical history and concomitant drugs).

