#### 2.4.2. Exclusion Criteria

(1)Participants with risk of suicide (scoring 2 or more points in BDI question 9, with specific suicidal thought or plan);(2)Participants with a history or present illness of severe psychiatric disorders (e.g., hallucination, delusion, etc., will be judged by a specialist in oriental neuropsychiatry or a resident who has been educated by a specialist in oriental neuropsychiatry and has clinical experience in neuropsychiatry of traditional Korean medicine for over 1 year) taking antipsychotic drugs to treat psychosis or receiving psychosis-related treatment;(3)Participants who have received Korean medical treatment or psychiatric treatment to improve symptoms of Hwa-Byung within the previous four weeks;(4)Seriously unstable medical conditions (the investigator will decide based on laboratory test, vital sign, etc.);(5)Participants with hyperthyroidism or hypothyroidism (over 1.5 times the upper reference limit or under 0.75 times the lower reference limit of TSH, Free T4, or taking medication due to hyperthyroidism or hypothyroidism);(6)Participants who are thought to be not appropriate to participate in this trial by the investigator.

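### The single sealed assignment table described in Section 2.4.4 does not assure concealment of later participants' assignments

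*Protocol article*

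**What the plan says.** Section 2.4.4 of the protocol article has the list produced by people "who are not involved in conducting and evaluating this clinical trial will generate a random assignment list in a specific and reproducible manner". Allocation "will be performed with a block randomization method in a 1:1:1 ratio". For custody, it says: "The random assignment table will be sealed and kept in a way that can be checked for unsealing, managed separately by the research manager". The sentence ends by placing this handling in the presence of the participants.

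On blinding, the same section says "The investigators and assessors will be separated so that the assessors will not know what kind of treatment the subjects have received", and then "It is not possible to maintain investigator blindness". Section 2.1 gives a single centre.

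On eligibility, Section 2.2 (Study Procedure) says "At visit 1, the investigator will check the results of the screening test", together with the physical examination and changes in history and medication. Random assignment is described in the next sentence. Two exclusion criteria in Section 2.4.2 rest on judgement: criterion 4 (seriously unstable medical conditions, decided by the investigator) and criterion 6, "Participants who are thought to be not appropriate to participate in this trial by the investigator".

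**The concern.** Generation of the list is independent. The weakness is in what happens to it afterwards. The article names one object (a table), one safeguard (a seal that shows whether it has been broken) and one holder (the research manager). Such a seal proves that nobody looked before the first allocation. From the second participant on, a broken seal is expected and so no longer tells anyone anything, unless further steps exist that the text does not mention.

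Concealment matters here because the people who judge eligibility know what earlier participants received. If they know or can guess the next assignment, they can bring a candidate forward, hold one back or use a discretionary exclusion. The groups would then differ at entry, which would affect the HB-M comparison of either therapy arm with control. Blinded assessors cannot undo that. Covariate adjustment removes only the part carried by measured variables, and Section 2.11.1 plans a t-test by default, with ANCOVA only if the baseline differs significantly.

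**Working it through.** The plan states no figure on this point, so there is none to reproduce. The check has two parts.

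**1. What the stated device protects**

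- Before the first allocation the table is sealed and the list was generated by uninvolved people. The sequence is concealed.
- At the first allocation the table must be consulted, which is its legitimate use.
- For participants 2 to 96, nothing in Section 2.4.4 covers the later rows: no individual envelopes, no remote release, no resealing. Protection depends on how the research manager handles the table, which is not described.
- For any one participant, the visit 1 check is described before assignment. The risk therefore concerns decisions about later candidates, not the person being randomised at that moment.

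**2. What blocks alone would reveal (illustration)**

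Inputs: 96 participants (Section 2.4.3), 1:1:1 blocks (Section 2.4.4), past assignments known to unblinded staff at one site. Assumptions: the block size is fixed and is known or inferred. The size is not stated, so 3, 6, 9 and 12 are used as a range.

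In a block of 3m with m places per arm, the next assignment is certain once only one arm has places left. The number of certain assignments in a block is therefore the length of its final run of a single arm. For a given arm, the 2m places of the other two arms cut the block into 2m + 1 gaps, and each of the m places of that arm is equally likely to fall in any gap. The expected number falling in the last gap is m/(2m + 1). Summed over three arms, this gives 3m/(2m + 1) certain assignments per block.

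| Block size | m | Certain per block, 3m/(2m + 1) | Complete blocks in 96 | Certain in total | Share of 96 |
|---|---|---|---|---|---|
| 3 | 1 | 3/3 = 1 | 32 | 32.0 | 33% |
| 6 | 2 | 6/5 = 1.2 | 16 | 19.2 | 20% |
| 9 | 3 | 9/7 = 1.286 | 10 | 12.9 | 13% |
| 12 | 4 | 12/9 = 1.333 | 8 | 10.7 | 11% |

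For blocks of 9, the six participants left over add none, because a final run of three can begin only at place 7. Simulation of 4,000 sequences per block size gave the same shares to within half a percentage point.

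The same simulation gave two looser measures. The share of assignments where it is certain whether the next one is control or not is 44%, 29%, 20% and 17%. The best guess of the arm is right 61%, 56%, 53% and 51% of the time, against 33% by chance.

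Varying the block size does not end guessing. If staff simply guess the arm used least so far, they are right about 55% of the time with random blocks of 3, 6 and 9, and about 53% with random blocks of 6, 9 and 12 (4,000 simulated sequences each).

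**The case against.** The strongest reply is that the text is unclear rather than wrong, and that the worst reading should not be taken as written. Much of this stands.

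- **Opening in front of participants.** A reader might infer that the table is opened there. The text says only "managed separately by the research manager in the presence of the participants", and the sentence is garbled.
- **Exposure of all later rows.** A reader might infer that after the first use up to 95 of the 96 assignments are known. That would require enrolling investigators to read the table. The article says custody is separate, and does not say that the research manager enrols participants, judges eligibility or shows the table to anyone.
- **Block size.** A journal article commonly leaves this to the full protocol (version 1.2, not shown), and keeping it from sites is good practice. Its absence is no error, and the article does not say that the blocks are of fixed size.
- **An open trial.** That label would be too broad, because assessors are separated and blind.
- **Bias in HB-M points or an inflated type I error.** Such figures can be produced only by assuming how strongly staff would steer candidates. The documents give no basis for any value, so none is offered here.

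What does not stand is the argument that the whole matter is detail left to the full protocol. The article does not leave concealment out. It states a device, and that device secures the sequence only up to its first use.

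**Conclusion.** The concern holds in a limited form. As described, a single sealed table held by the research manager does not assure that later participants' assignments are concealed. One site, unblinded investigators, blocks and discretionary exclusions make this matter. The documents do not show that anyone who enrols participants sees the table, so this is a weakness of the stated safeguard and not evidence of a breach.

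The only size that can be given is conditional. With a fixed block size known to or inferred by staff, between 11% (blocks of 12) and 33% (blocks of 3) of assignments could be known with certainty. The effect on the HB-M comparison cannot be quantified from the documents. The change is worth making because it is cheap and removes the dependence on how one table is handled.

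**What to change.** In Section 2.4.4:

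1. Replace the single sealed table. The independent person who already generates the list keeps it and releases one assignment at a time (by telephone, e-mail or web form). Sequentially numbered, opaque, individually sealed envelopes prepared by that person are an acceptable alternative.
2. State that an assignment is released, or an envelope opened, only after final eligibility is signed off and the enrolment code (DJ-E-ZZZ) is recorded. Say who does each step.
3. Remove the handling of the table in the presence of participants.
4. Generate the list with block sizes that vary at random (for example 6, 9 and 12) and are not disclosed to site staff. This is a secondary measure: it reduces certain predictions but does not end guessing. The main gain comes from item 1.

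The cost is a change of wording and 96 messages or envelopes, one per participant, with a short wait at visit 1. Group sizes may end slightly unequal. No extra participants are needed.

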### 2.5. Interventions

The ETE group (experimental group 1) and VR-based ETE group (experimental group 2) will receive ETE two times per week for the first four weeks and once a week for the next four weeks (a total of 12 times). The daily management group (control group) will receive Hwa-Byung management training materials and wait for eight weeks living a daily life. Hwa-Byung management training materials will be the same for the experimental and control groups.

ETE will be performed by a specialist in oriental neuropsychiatry or a resident who has been educated by a specialist in oriental neuropsychiatry and has over one year of clinical experience in neuropsychiatry of traditional Korean medicine.

We will follow the ETE protocol [17]. It consists of five stages: (1) assessment of emotion and physical symptoms (CSEI-S, Mentalizing the Room of Mind (MRM), SUDS); (2) analyze the relationship between emotion and physical symptoms, analyzing emotion and sensation with oriental neuropsychiatric perspective, and finding core emotion; (3) training—depending on the patient’s emotional state, choose from exposure mindfulness meditation, breathing meditation, somatic mindfulness meditation, upper danjeon meditation, joy meditation, lower danjeon meditation, middle danjeon meditation, resource mindfulness meditation, and integrated-triple danjeon meditation; (4) assessment of emotion and physical symptoms after intervention (CSEI-S, MRM, SUDS); and (5) managing emotion education.

In the analyzing stage, it is essential to identify the core emotions of the participants, as these will inform the selection of the most appropriate mindfulness meditation types for the training stage. Based on the identified core emotion, a targeted objective and desired emotional response will be established to enhance the effectiveness of the meditation practice. For example, to address emotions like fear and surprise, breathing meditation will be used to enhance concentration, somatic mindfulness meditation to increase sensory awareness, and upper danjeon meditation to foster insight. For sadness and depression, joy meditation will be employed to encourage positive emotional responses, and lower danjeon meditation to explore life meaning by engaging emotions beyond sadness. To address anger, middle danjeon meditation will be used to cultivate compassion, and resource mindfulness meditation to elicit alternative emotional responses. Additionally, integrated-triple danjeon meditation will be applied to integrate and harmonize emotions, supporting emotional stability.

VR-based ETE will follow the above ETE protocol using head-mounted displays (HMDs) or virtual reality software implemented with computers and project sets. The VR software (Mentalcare-PV02), developed by the company Joygram specifically for this study, is installed and run on an HP Victus Desktop 15L TH02-0001kr (R5-5600G/RTX3060Ti/32GB/1TB) (manufactured by HP Inc. in China, Brazil, India, or Mexico), and uses the Oculus Quest 2 (manufactured by META (formerly Facebook) in China) as the primary VR headset. With this VR setting, subjects will conduct training to stabilize their emotions with opposing emotions for problem emotions in a virtual environment that is not limited to the clinical environment.

### 2.6. Criteria for Concomitant Drugs

#### 2.6.1. Possible Drugs

It is permissible if a dose of psychiatric drugs (e.g., anti-depressants, anti-anxiety medication, tranquilizers, and sleeping pills) is constant for 4 weeks before participating in the trial. However, when taking drugs, the history of the drug is investigated at the time of the visit, and if there is a change in the type and dose of the drug, it is used as a side effect variable or a correction variable. Drugs for transient care of other diseases will be medicated after confirmation by the researcher. When concomitant drugs, including drugs for other diseases or adverse events, are administered, information about the drugs, including name, purpose, dose, and duration, will be recorded in a progress note.

#### 2.6.2. Prohibited Drugs

There are no specific drugs prohibited from concomitant use, but the drugs that may affect results can be prohibited at the discretion of the researchers’ decision (e.g., starting with new medications, such as anti-depressants, anti-anxiety drugs, anti-psychotics, corticosteroids, female hormones, L-dopa, digitalis, bromide, cyclosporin, disulfiram, isoniazid, and yohimbine, during the clinical trial). Participants will be required to maintain a stable treatment regimen throughout the study period. Initiation of any new treatments, including additional medications or therapeutic interventions outside of the ETE, will result in withdrawal from the study. This criterion is intended to isolate the effects of the ETE intervention on Hwa-Byung symptoms and prevent confounding results from other treatments.

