Additional visits may be made at any time other than the scheduled visit when deemed necessary at the request of the subject or discretion of the researcher. If a subject visits on an unscheduled day, adverse reactions, concomitant medications, results of tests performed, and subsequent medical treatment must be recorded in the case record. Even in the case of subjects who drop out, laboratory tests, pregnancy diagnostic tests, and efficacy evaluation tests can be performed during additional visits.

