#### 2.8.2. Dropout

Subjects will be dropped if they fail to complete the trial due to adverse events or other reasons. The investigator can stop the interventions and tests and drop the subjects from the trial, or the subjects can always drop out of the trial with their own free will. The subjects may be dropped in the following cases: severe adverse events occurred to the subjects; difficulty proceeding with the trial due to adverse events; discovering systemic disease that was not detected in the pre-intervention examination; the subject or a legal representative of the subject requests to stop the trial due to unsatisfaction; the subject does not comply with the instructions of the investigator; the subject withdraws consent to participate in the trial; the subject cannot be tracked to follow-up; the subject is prescribed a treatment that can affect the study result, without the direction or consent of the investigator during the trial period or follow-up period; progression of the trial is considered inappropriate by the investigator.

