### 2.10. Statistical Analysis

Efficacy analysis will be evaluated primarily based on the Full Analysis Set (FAS) principle and secondarily according to the Per-Protocol (PP) principle of the primary outcome. Missing values will be imputed appropriately according to why they occur. Subjects are excluded from FAS analysis in following cases: failure to meet eligible criteria, no intervention specified in the clinical study plan has been received, no data have been collected because they have never been evaluated since randomization. Subjects will be excluded from the per-protocol (PP) analysis if they meet any of the following conditions: 1. Dropped out during the trial. 2. Violated the inclusion or exclusion criteria. 3. Had less than 75% compliance with the overall intervention. Additionally, other serious violations of the study protocol may also be considered as grounds for exclusion from the PP analysis. The demographic data of the study subjects included in this trial and baseline clinical history data will be presented with mean and standard deviation (SD) for continuous data for each group and frequency and percentage for categorical data. For each group, an independent sample t-test or Wilcoxon rank sum test will be performed depending on normality in the case of continuous variables, and for categorical variables, a Pearson chi-square test or Fisher’s practice test will be performed.

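### Section 2.6.2 makes starting any new treatment a reason to leave the study, which contradicts 2.6.1 and 2.8.2, and outcome assessment afterwards is only optional

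*Protocol article*

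**What the plan says.** The rules on concomitant treatment stand in three sections of the protocol article.

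- **2.6.1 (Possible Drugs).** Psychiatric drugs at a constant dose for four weeks before entry are permitted. For later changes, "if there is a change in the type and dose of the drug, it is used as a side effect variable or a correction variable". For other illnesses, "Drugs for transient care of other diseases will be medicated after confirmation by the researcher". Drugs given for adverse events are to be recorded.
- **2.6.2 (Prohibited Drugs).** It opens by saying that no specific drug is prohibited, but that "the drugs that may affect results can be prohibited at the discretion of the" researchers. It then sets a mandatory rule: "Initiation of any new treatments, including additional medications or therapeutic interventions outside of the ETE, will result in withdrawal from the study". The stated purpose is to isolate the effect of ETE.
- **2.8.2 (Dropout).** The list of grounds is introduced by "The subjects may be dropped in the following cases". The treatment-related ground covers a treatment that can affect the study result and was prescribed "without the direction or consent of the investigator during the trial period or follow-up period".

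Three further sections determine what follows for the analysis. Section 2.2 says that for patients who drop out, "efficacy evaluation tests can be performed during additional visits". Section 2.10 makes FAS primary and PP secondary, and its first PP exclusion is "Dropped out during the trial". Section 2.11.2 analyses CSEI-S, PHQ-15, SRI, BDI, STAXI, STAI, fNIRS and HRV by PP with no handling of missing values.

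**The concern.** The same patient can stay or leave depending on which section the site follows. An analysis plan cannot repair this later, because the decision is taken at the visit.

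The statistical problem is the consequence of leaving. Starting a new treatment happens after randomisation, and patients who are doing badly may be more likely to do it. Controls receive only training materials and wait eight weeks (2.5), so they may seek other treatment more often than patients in the two ETE arms. If such patients are withdrawn and not assessed again, the comparisons of ETE and VR-based ETE with control rest on imputed values (FAS) or on a selected subset (PP). VR-based ETE versus ETE is less exposed, because both arms are treated.

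**Working it through.** **Step 1: the same event under each section.**

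| Event during the trial | 2.6.1 | 2.6.2 | 2.8.2 |
|---|---|---|---|
| Confirmed short-term drug for another illness | Allowed | Withdrawal | No treatment-based ground, since the researcher confirmed it |
| Drug for an adverse event | Recorded | Withdrawal | No treatment-based ground if the investigator directed it |
| Switch of psychiatric drug type | Used as a variable, which presupposes that the patient's data are kept | Withdrawal, if a switch counts as initiation | Optional, and only if it can affect the result and lacked consent |
| Dose change of an existing drug | As above | Not clearly initiation | As above |
| New Hwa-Byung-relevant treatment | Not addressed | Prohibition discretionary in the opening, withdrawal mandatory later | Optional, and only if without direction or consent |

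Rows 1 and 2 are plain contradictions. Row 3 is arguable. Row 4 is not a conflict. In row 5 the sections differ on whether withdrawal is mandatory.

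**Step 2: what data remain after withdrawal.** Section 2.2 schedules HB-M at visits 1, 12 and 13. A patient withdrawn before visit 12 and not recalled has only a baseline score. Withdrawal is not among the FAS exclusions in 2.10, and 2.11.1 accepts a patient with at least one intervention and one score. The FAS therefore keeps the patient and must impute.

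**Step 3: what PP does.** A withdrawn patient is a dropout and leaves PP even if assessed later. For the eight measures in 2.11.2, PP is the only analysis set named. HB-M at 16 weeks is not among those eight.

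**Step 4: size.** The plan gives no rate of starting treatment. The 25% dropout allowance in 2.4.3 is not split by arm or reason. The following is purely illustrative and concerns only the PP analysis of the eight secondary measures.

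Assume that a fraction f of an arm starts treatment and that these patients lie d SD below their arm mean. Excluding them raises that arm's mean by d × f/(1 − f). The treated-minus-control difference therefore shrinks by

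d × [fc/(1 − fc) − fa/(1 − fa)],

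where fc is the control fraction and fa the treated fraction. With fa = 0.05, fa/(1 − fa) = 0.053.

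| fc | fc/(1 − fc) | Shrinkage, d = 0.5 | Shrinkage, d = 1 |
|---|---|---|---|
| 0.10 | 0.111 | 0.03 SD | 0.06 SD |
| 0.15 | 0.176 | 0.06 SD | 0.12 SD |
| 0.20 | 0.250 | 0.10 SD | 0.20 SD |

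Equal fractions and deficits give 0. With fa = 0.10 and fc = 0.05 the sign reverses (−0.03 and −0.06 SD). For scale, the standard error of a difference is √(2/32) = 0.25 SD with 32 per arm, or √(2/24) = 0.29 SD with the 24 per arm left after 25% dropout (32 × 0.75 = 24). Every shift shown is smaller than one standard error, but it would be systematic, not random.

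**The case against.** Read together, the sections suggest a workable rule: confirmed transient care stays, and symptom-relevant new treatment leaves. The purpose stated in 2.6.2 and the limits in 2.8.2 both point that way, so the breadth of 2.6.2 may be loose drafting. That is probably the intention, but the mandatory sentence carries no exception, and site staff should not have to infer one.

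Replacing one permitted drug by another is not clearly initiation or an addition. This stands, and it is why the switch is called arguable. An optional list in 2.8.2 is also not strictly incompatible with a mandatory rule for one ground. However, 2.8.2 narrows that ground to unapproved, result-affecting treatment, and 2.6.2 does not.

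Withdrawing treatment starters in order to isolate ETE is a choice of question, not an error in itself. This stands too, and the fix therefore keeps an analysis for that aim. It is also fair that the full protocol may say more about assessment after dropout. The article nonetheless states a permissive rule.

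A reader might go further and infer that the primary result is biased, or that withdrawn patients are excluded from it. The documents do not support that: withdrawal is not an FAS exclusion, and the effect depends on the imputation and on who is reassessed. Nor do they support a direction of bias, since no rates by arm are given. A reader might also take the correction variable in 2.6.1 to be a covariate in the efficacy models. That is possible, but the term is not defined.

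**Conclusion.** The point holds as a contradiction in the withdrawal rule with a consequence for the analysis. Section 2.6.2 conflicts plainly with 2.6.1 over confirmed transient-care and adverse-event drugs, and with 2.8.2 over whether and when a patient is dropped. Followed literally, it turns a post-randomisation event that may be related to outcome into loss from the study, with later efficacy data optional. The primary FAS then needs imputation where scores could have been observed, and the eight PP-analysed secondary measures lose these patients.

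Size and direction are unknown. Bias requires that starting treatment relates to outcome and that its frequency or its relation to outcome differs between arms. Both are plausible with a waiting control, and neither is shown. The illustrative shifts of 0.03 to 0.20 SD depend wholly on assumed rates and deficits, bear only on the choice of PP for the secondary measures, and say nothing about the primary analysis.

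**What to change.** 1. **One rule across 2.6.1, 2.6.2 and 2.8.2.** Exempt confirmed transient-care and adverse-event drugs. Make a new Hwa-Byung-relevant treatment a reason to stop the study intervention, not to leave the study. Say explicitly how a switch of psychiatric drug is handled.
2. **Section 2.2.** Replace the permissive wording by a requirement that the efficacy assessments scheduled at weeks 8 and 16 will be done in all patients who still consent, and use those observed scores in the FAS.
3. **Section 2.11.2.** Make FAS the main analysis of the eight listed measures, with missing values handled, and PP supportive. Without this, the PP exclusion remains whatever is done under items 1 and 2. Because these patients would no longer count as dropouts, 2.10 should name the start of such a treatment as a PP exclusion.
4. **Efficacy models.** Do not adjust for drug changes after randomisation. Report them descriptively.

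The cost is protocol wording and a few extra assessments at visits already planned. The FAS estimate would include the effect of any new treatment, which is a different question from isolating ETE. PP stays as the supportive analysis for that aim, open to selection bias, and the investigators should state the choice.
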